### Inclusion Criteria

Patients undergoing uncomplicated cataract surgery at Reiyukai Eiko Masunaga Eye Hospital irrespective of the type of surgery (SICS or phacoemulsification) will be included in the study.

### Exclusion Criteria

Patients will be excluded if (1) there are complications during the surgery that warrant more frequent follow-up visits (eg, premature entry, posterior capsular rupture, zonular dialysis, postoperative hyphema, toxic anterior segment syndrome, or postoperative fibrin in the anterior chamber); (2) the surgery is for complicated cataract, traumatic cataract, ocular hypertension, or if the patient has drug allergies; (3) the patients has a history of diseases that might affect postoperative visual outcomes, such as uveitis, glaucoma, viral keratitis, corneal scarring, hypertensive retinopathy, diabetic retinopathy, central retinal vein occlusion, branched retinal vein occlusion, or age-related macular degeneration; (4) the patient is unwilling to participate or does not provide written consent; and (5) the patient misses the follow-up visits.

### Sample Size and Sampling Technique

Sample size is calculated as follows: 2[Zα + Z1 – β] 2 × (sd2/d2) = 2 [1.96 + 1.645 ] 2 × [(0.1125)2/(0.025)2] = 263 for one group, where reference mean values for postoperative visual outcomes are taken from the study conducted by Deshpande et al [25]. The number of participants in intervention group will be 263 and the number of participants in the control (reference) group will be 263. We will use a random sampling technique and computer-generated random numbers to assign patients to the intervention or control group. We generated randomized numbers with a commonly used method [26]. The assignment will be done by the counsellor on the first postoperative day. The researchers will be masked as to randomization at all postoperative visits.

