## Methods

### Study Design, Setting, and Participants

This will be a prospective, quantitative, experimental, noninferiority control study of health services use. Selected patients undergoing cataract surgery at Reiyukai Eiko Masunaga Eye Hospital irrespective of the type of surgery (SICS or phacoemulsification) will be included in the study.

All enrolled patients will undergo an examination on the first postoperative day conducted by an ophthalmologist who is unaware of the patient’s group assignment. Subsequently, the patient will proceed to the counselor’s office, where a unique identification number will be generated and the patient will be randomized into either group 1 or group 2.

In group 1, patients will be instructed to attend follow-up visits at 1 week and 1 month postoperatively. In group 2, patients will be instructed to attend a follow-up visit at 1 month postoperatively only. During the visit, the patients will receive detailed guidance on the appropriate use of medications and be educated about the signs and symptoms they should be vigilant for. The specific date of the postoperative visit will also be communicated.

At each follow-up visit, the patient will directly visit the counselor’s office. Upon arrival, they will be provided with a blank sheet of paper containing the unique identification number assigned to them on the first postoperative day. Visual acuity testing will be conducted by a blinded optometrist, while slit lamp biomicroscopy will be performed by a blinded ophthalmologist. Before leaving the hospital, the patient will return the paper to the counselor, who will then enter the necessary information into the patient’s file. 

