## Results

More than 526 participants will be enrolled in the study, with a minimum of 263 assigned to the intervention group (deferred follow-up visits) and a minimum of 263 to the comparison group (standard practice of early postoperative follow-up visits). The sample will have diverse demographics, ensuring a representative population.

Visual acuity measurements will be obtained for both groups during the follow-up period. We will be able to statistically compute whether the deferred follow-up visit group demonstrates comparable visual acuity outcomes to the comparison group. This will be inferred if there are no statistically significant differences between the two groups in terms of visual acuity outcomes (*P*>.05).

Among the participants in the deferred follow-up visit group, the number of patients who experience postoperative complications during the 4-week follow-up period will be compared with the group with the 1-week follow up visit.

We will also determine if participants in the deferred follow-up visit group report high levels of satisfaction with the extended recovery period and reduced travel burden. The number of participants who express that deferring follow-up visits provided them with convenience and comfort during the recovery phase will be mentioned.

We will determine if reduction in early postoperative visits allows health care providers to allocate their time and expertise more efficiently, focusing on patients with immediate needs or complex postoperative care requirements.

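### The printed sample-size formula gives 526 per group, not 263, so at 263 per group the power is about 72% rather than the 95% its inputs imply

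*Protocol article*

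**What the plan says.** The protocol article, under Sample Size and Sampling Technique, gives the formula in symbols as "2[Zα + Z1 – β] 2 × (sd2/d2", where the 2s that follow a bracket or a term are squares. It then puts in 1.96, 1.645, an SD of 0.1125 and d = 0.025, and the line closes with "0.1125)2/(0.025)2] = 263 for one group". The reference values are attributed to an earlier study of deferred follow-up.

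The same section applies the result to both arms: "The number of participants in intervention group will be 263 and the number of participants in the control (reference) group will be 263". The Results section repeats it: "More than 526 participants will be enrolled in the study, with a minimum of 263 assigned to the intervention group".

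Two other statements bear on the consequences. Study Design, Setting, and Participants calls the trial a "prospective, quantitative, experimental, noninferiority control study". The Results section will infer comparable outcomes if there are "no statistically significant differences between the two groups in terms of visual acuity outcomes", with P>.05 as the criterion.

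**The concern.** The formula, the inputs and the result stand together in one line, and the result does not follow from the other two. The stated 263 is half of what the line evaluates to, yet it is labelled as the size of a single group and used for both arms.

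The power that the inputs specify is therefore not delivered. This matters more than usual because of how the trial will be read. Under the P>.05 rule in the Results section, a shortage of patients makes the hoped-for conclusion easier to reach. If deferral really worsened acuity by the 0.025 used for planning, a trial of half the intended size would more often find no significant difference and call the groups comparable. Under a non-inferiority analysis the harm runs the other way: the trial would more often fail to show non-inferiority when the two schedules are truly equivalent.

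**Working it through.** **Inputs**, all from Sample Size and Sampling Technique:

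- z for alpha: 1.96 (two-sided 5% or one-sided 2.5%)
- z for power: 1.645 (corresponds to 95%)
- SD: 0.1125
- d: 0.025
- allocation: 1:1, 263 per group

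**Step 1. The printed formula.**

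- (1.96 + 1.645)² = 3.605² = 12.996
- (0.1125/0.025)² = 4.5² = 20.25
- 12.996 × 20.25 = 263.17
- 2 × 263.17 = 526.34 per group, or 527 rounded up; 2 × 527 = 1,054 in total

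The plan's 263 is reproduced exactly by the third line, that is, without the leading 2.

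**Step 2. Whether another reading gives 263 per group.** Patients per group for d = 0.025 and SD 0.1125:

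| Reading | n per group |
|---|---|
| Bracket not squared | 146 |
| Two-sided 5% (or one-sided 2.5%), power 80% / 90% / 95% | 318 / 426 / 527 |
| One-sided 5%, power 80% / 90% / 95% | 251 / 347 / 439 |
| Non-inferiority, one-sided 2.5%, power 95%, true difference 0 | 527 |
| z-values swapped (one-sided 5%, power 97.5%) | 527 |
| One-sided 10%, power 90% | 267 |

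Only the last row comes close to 263, and its z-values (1.28 and 1.28) are not the printed ones.

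**Step 3. Power at 263 per group.**

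- SE = 0.1125 × √(2/263) = 0.00981
- 0.025/0.00981 = 2.548
- Power with z = 1.96: Φ(2.548 − 1.96) = Φ(0.588) = 72.2% (72.0% with the t distribution)
- Power with z = 1.645 (one-sided 5%): Φ(2.548 − 1.645) = Φ(0.903) = 81.7%
- Check at 526 per group with z = 1.96: 95.0%

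The 72% applies both to detecting a true difference of 0.025 at two-sided 5% and to showing non-inferiority with a margin of 0.025 at one-sided 2.5% when the true difference is zero.

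**Step 4. What 263 per group would support at 95% power.**

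- Difference: 3.605 × 0.00981 = 0.0354, which is 41% larger than 0.025 (0.0354/0.025 = 1.41)
- Or, keeping d = 0.025, an SD of about 0.080 instead of 0.1125

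**Step 5. Consequence under the P>.05 rule.** With a true difference of 0.025, the chance of a non-significant result is 1 − 0.722 = 27.8% at 263 per group, against 5% at 526 per group.

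**Step 6. Effect of losses (assumed).** The article gives no loss rate, and the printed calculation has no allowance for one, although the exclusion criteria remove patients who miss follow-up visits. If those patients are not replaced:

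- 10% loss: 237 per group, SE = 0.1125 × √(2/237) = 0.01033, power Φ(2.419 − 1.96) = 68%
- 20% loss: 210 per group, SE = 0.1125 × √(2/210) = 0.01098, power Φ(2.277 − 1.96) = 62%

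**The case against.** The arithmetic itself has no good defence. The leading 2 stands in both the symbolic and the numeric form, so it is unlikely to be a typesetting accident. The number 263 cannot be meant as a total, because it is assigned to each arm. Nor is this a detail that an article leaves to a fuller document, since the article prints the formula, the inputs and the answer.

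The fair objections concern how much may be claimed from it:

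- **Power is not stated in words.** The 95% is read from 1.645 standing in the power position, and alpha likewise from 1.96. This stands as a caveat. If the two values were swapped, the formula would still give 526 per group, and power at 263 would be about 82% instead of the 97.5% then implied.
- **263 is a minimum.** The Results section speaks of more than 526 patients in total, so 72% is the power at the floor. This also stands, but no higher target is given, and nothing suggests enrolment near 1,054.
- **The article does not say what d is.** It could be a difference to detect or a non-inferiority margin. The 72% is the same either way, but the consequences differ, as set out above.
- **The figure of 0.035 is not a margin.** It describes what 263 per group could resolve. The abstract says the minimum clinically important difference will be set from Snellen improvement, so a margin chosen to fit the available number would lack a clinical basis. This objection limits the remedy.

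None of these changes the error or its size.

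**Conclusion.** The concern holds. From its own formula and inputs the trial needs 526.3 patients per group (527 rounded up, 1,054 in total), and the article plans 263 per group. At that number the power for d = 0.025 is about 72%, not the 95% implied by the inputs, and the risk of missing such a difference is about 28% instead of 5%.

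This rests on the printed SD of 0.1125, on 1.96 as the alpha term and 1.645 as the power term, on 263 analysed patients in each arm and, for the non-inferiority reading, on a true difference of zero. With a one-sided 5% test the power would be about 82%, still well short. Any unreplaced losses lower these figures. That the formula's 526 was taken for a total and then halved is a plausible explanation, but it is an inference.

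**What to change.** In Sample Size and Sampling Technique, correct the result of the printed line to 526.3, that is 527 per group after rounding up, and state alpha, power and the meaning of d in words. Then take one of two courses:

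- **Enrol to the corrected number.** This means about 1,054 patients in total, roughly double the present plan, with a matching extension of the recruitment period.
- **Keep 263 per group and restate the design.** Say that 263 per group gives about 72% power for a difference of 0.025, with SD 0.1125 and two-sided 5% (one-sided 2.5%). The value 0.035 may be reported as the difference for which 263 per group has 95% power, but it should not be adopted as a margin unless it is justified clinically.

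Either way, carry the corrected figure into the Results section and the eventual report, and say whether patients who miss visits are replaced. The second course costs one corrected number and one restated sentence and needs no extra patients. The first costs the additional enrolment.

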**Methods:**

A prospective, quantitative, experimental control study will be carried out in Reiyukai Eiko Masunaga Eye Hospital, located in Banepa, Kavrepalanchok, Nepal. All patients undergoing cataract surgery meeting the inclusion and exclusion criteria irrespective of the type of surgery (small-incision cataract surgery or phacoemulsification) will be included in the study. The patients will be randomly assigned to 1 of 2 groups. Patients in group 1 will be examined on day 1, day 7, and day 30, whereas patients in group 2 will be examined on day 1 and once between days 25 to 30. The minimum clinically important difference (MCID) in our study will be set according to the improvement in the Snellen visual acuity chart.

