Limburg et al [9] investigated the benefits of postoperative follow-up in India and concluded that visual acuity at hospital discharge was not representative of visual acuity several weeks after surgery [10]. However, a study by Congdon et al [11] concluded that early vision assessment of all patients and a follow-up assessment only for patients who return to the clinic without prompting were adequate to ensure the quality of cataract surgical services. This is again countered by a study by Gupta et al [12], who presented evidence of substantial changes between visual acuity on the first postoperative day and at subsequent follow-up. Postoperative complications and uncorrected refractive errors are 2 major issues that lead to poor visual outcomes [5,13-16]. Both issues can be wholly addressed by promoting and ensuring postoperative follow-up at the designated time [17-20]. As per the National Programme of Control of Blindness, Vision 2020: Right to Sight, the recommended postoperative follow‑up visit schedule is a first follow‑up on the first postoperative day by the surgeon (mandatory), a second follow‑up between day 7 and day 10, and a third follow‑up (with refractive correction) between day 30 and day 45 [21]. Saeed et al [22] and Tinley et al [23] concluded that postoperative follow‑up visits can be safely deferred up to 2 weeks after cataract surgery, thereby enhancing the efficiency of day care units. Meltzer et al [24] performed a study using data from the PRECOG (Prospective Review of Early Cataract Outcomes and Grading) trial and reported that visual acuity immediately after cataract surgery was highly correlated with visual acuity after 40 days, suggesting that for the purposes of quality assessment, follow‑up of all patients is not needed. A study by Deshpande et al [25] concluded that visual outcomes after uneventful cataract surgery were comparable between patients followed up on days 3 to 7 and days 25 to 30 in comparison to patients directly followed up on days 25 to 30. Additionally, it was observed that the first follow‑up visit could be safely deferred until 4 weeks after uneventful cataract surgery, including phacoemulsification or small-incision cataract surgery (SICS), in patients with no preexisting ocular or systemic comorbidity [25]. The purpose of this study is to evaluate, from a safety perspective, altering the standard postoperative management guidelines after cataract surgery so that the first follow‑up visit at 1 week is deferred in patients with no significant preexisting ocular or systemic comorbidity and no intraoperative surgical complications or immediate postoperative complications at the time of discharge from the hospital.

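### The noninferiority trial is sized on a difference of 0.025 that is not identified as a margin or an expected difference; if it is the cited study's arm difference, repeating that study would fail the P>.05 rule

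*Protocol article*

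**What the plan says.** The Study Design section states: "This will be a prospective, quantitative, experimental, noninferiority control study of health services use".

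The Sample Size section prints a two-mean formula with multipliers 1.96 and 1.645, ending "0.1125)2/(0.025)2] = 263 for one group". The same size is then given to both arms: "The number of participants in intervention group will be 263 and the number of participants in the control (reference) group will be 263". The only source named for the inputs is in the clause "where reference mean values for postoperative visual outcomes are taken from the study conducted by" an earlier study of deferred follow-up. The section does not print those means. It gives 0.025 no unit or direction, and does not call it a margin, an expected difference or a clinically important difference.

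The Background says that the same earlier study "concluded that visual outcomes after uneventful cataract surgery were comparable between patients followed up on days 3 to 7 and days 25 to 30", as against patients seen only at days 25 to 30.

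A clinical threshold appears only in the abstract: "The minimum clinically important difference (MCID) in our study will be set according to the improvement in the Snellen visual acuity chart". It has no value and no stated link to 0.025.

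The Results section gives the decision rule for comparable acuity: "This will be inferred if there are no statistically significant differences between the two groups in terms of visual acuity outcomes", with P>.05 as the criterion.

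**The concern.** A noninferiority sample size rests on two separate quantities: the margin (the deficit to be ruled out) and the expected true difference. The quantity in the denominator is the margin minus the expected difference. The article supplies one number of undefined status.

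The sourcing clause points towards an expected difference. The formula takes two data inputs, an SD and a difference, and means can enter it only through the difference. It is therefore natural to read 0.025 as the gap between the earlier study's arm means. On that reading, the trial is built to detect a difference that its own Background reports as comparable, and detecting it then counts against deferral.

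Two things are at stake. A result matching the supporting study could be reported as a failure to show comparability. And the reader cannot tell what deficit the trial is able to exclude.

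**Working it through.** **Inputs.** From the Sample Size section: SD = 0.1125; d = 0.025; z-values 1.96 (two-sided 5%, or one-sided 2.5%) and 1.645 (95% power); 263 per arm. From the Results section: comparability if P>.05. The normal approximation is used throughout.

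**1. The plan's own figure.**
- (1.96 + 1.645)² = 12.996 and (0.1125/0.025)² = 20.25.
- With the printed leading factor 2: 2 × 12.996 × 20.25 = 526.3 per arm.
- Without it: 12.996 × 20.25 = 263.2. The stated 263 per group appears only when the factor 2 is dropped.

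**2. Standard error at the stated size.** SE = 0.1125 × √(2/263) = 0.00981.

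**3. Reading A: 0.025 is the earlier study's arm difference (assumed).**
- Exact repeat: z = 0.025/0.00981 = 2.55, P = 0.011, 95% CI 0.006 to 0.044. The P>.05 rule is not met.
- Smallest observed difference that fails the rule: 1.96 × 0.00981 = 0.019.
- SD above which a repeated 0.025 would no longer fail: 0.025/(1.96 × √(2/263)) = 0.146.
- If 0.025 is the true difference, the probability of P<.05 is Φ(2.55 − 1.96) = 72% at 263 per arm. At 527 per arm, the size the formula requires, it is 95%.
- The same repeated result has an upper limit of 0.044. It would meet a margin of 0.05 (an illustration, not a figure from the article) but not a margin of 0.025.

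**4. Reading B: 0.025 is the margin and the expected difference is zero.** The printed formula is then the standard noninferiority form. Power at 263 per arm, one-sided 2.5%, is Φ((0.025 − true deficit)/0.00981 − 1.96):

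| True deficit with deferral | Power |
|---|---|
| 0.025 (worse) | 2.5% |
| 0.0125 (worse) | 25% |
| 0 | 72% |
| −0.025 (better) | 99.9% |

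Power at equality is 72%, against the 95% implied by 1.645.

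**5. What 263 per arm can exclude with 95% power.**
- True difference zero: (1.96 + 1.645) × 0.00981 = 0.035.
- Deferral truly worse by 0.025: 0.035 + 0.025 = 0.060.

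**The case against.** A reader might infer that 0.025 is certainly the earlier study's arm difference, so that a repeat of that study is bound to be called not comparable. The documents do not support this. The article attributes only mean values to that study. It prints none of them and never calls 0.025 observed or expected. The figure could be a chosen difference, or a fraction of one reference mean, or the clause could be a loose description of where the inputs, including the SD, came from. The Background reports a conclusion of comparability without a number, so it does not show that 0.025 was judged unimportant. Even on the assumption, failure is certain only for an exactly repeated difference with an SD below about 0.146.

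A second tempting inference is that 0.025 cannot serve as the margin. That holds only if deferral is truly worse by that amount, which the article does not state. With zero expected difference the formula has the correct noninferiority form, and the design label supports that reading.

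It is also fair to say that the P>.05 rule penalises any non-zero true difference as the sample grows, wherever 0.025 came from.

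These objections make the claim about the origin of 0.025 conditional. They leave three things standing: 0.025 has no stated status, no margin has a value, and 263 per arm does not deliver 95% power at 0.025.

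**Conclusion.** The point holds in conditional form. A trial labelled noninferiority is sized on one number not identified as a margin, its clinically important difference has no value, and comparability is inferred from a non-significant test.

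- **If 0.025 is the earlier study's arm difference:** an exact repeat fails the rule at P = 0.011, and a true difference of 0.025 fails it about 72% of the time at 263 per arm. This rests on the natural but unconfirmed reading of the sourcing clause and on an SD near 0.1125.
- **If 0.025 is the margin with zero expected difference:** the formula is of the right kind, but the stated size gives 72% power because it is half of what the printed formula yields.

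On either reading the Sample Size paragraph misstates what the trial can establish. The direction and unit of 0.025 are not given, so whether a repeat would favour or disfavour deferral is unknown.

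**What to change.** In the Sample Size section:
- State what 0.025 is, with its unit and direction.
- Fix a noninferiority margin on clinical grounds before enrolment, separately from any expected difference, and use d = margin minus expected difference.
- If enrolment stays as planned, restate its capability: with SD 0.1125, 263 per arm excludes a deficit of about 0.035 with 95% power if the true difference is zero. The figure of about 0.060 applies only if deferral is assumed truly worse by 0.025, and should carry that condition.

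In the Results section, replace the P>.05 rule with a comparison of the confidence interval for the acuity difference against the margin.

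The cost is rewording and a documented choice of margin, with no extra patients if enrolment is kept. The downside is a less favourable stated figure, about 0.035 in place of 0.025. If the chosen margin is tighter than 263 per arm can exclude, the protocol would have to accept lower power or a larger trial.
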